## Discussion

The AHF-Voice study has been designed to provide new insights into the etiology, characteristics, determinants, progression, and prognostic utility of vocal biomarkers in patients experiencing an episode of AHF. Smartphone-based daily voice recordings are used as a substrate to detect subtle vocal changes, which are then associated with conventional markers of congestion.

The AHF-Voice study cohort represents a well-phenotyped population of patients with AHF. It comprises a high proportion of patients with NYHA functional class III and IV at admission, indicating a substantial number of patients with significant congestion. The cohort includes a significant proportion of patients with *de novo* HF and an even distribution between heart failure with a reduced or mildly reduced ejection fraction and HFpEF. The profound differences between LVEF-based HF phenotypes (31) will allow for stratified analyses, thereby exploring potential voice-based differences between these HF subtypes. Furthermore, a substantial number of voice recordings were collected during the index hospitalization and will be collected during follow-up period, enabling the application of advanced artificial intelligence methodologies for predictive modeling.

Changes of vocal biomarkers over time and their determinants remain under-researched. Previous studies only suggested the existence of distinct vocal biomarker patterns in individuals exhibiting either congested or decongested states (13, 15). To address this gap, the AHF-Voice study will investigate the longitudinal trajectories of vocal biomarkers in patients with AHF through daily voice recordings, both during the course of their hospitalization and over a 6-month observation period. This approach will facilitate a comprehensive assessment of vocal changes in relation to disease progression and patient outcomes, thereby contributing to the development of more personalized and predictive care strategies for patient with AHF.

According to the European Laryngological Society (ELS) and the American Speech-Language-Hearing Association, a comprehensive voice assessment for general voice impairments in the field of phoniatrics is suggested (32, 33). The AHF-Voice study will be the first to comprehensively examine all four (auditory, visual, physician-reported, and patient-reported) dimensions of the human voice: (i) vocal characteristics are captured through the recording of various voice tasks; (ii) visual assessment of the vocal cords is conducted using video-laryngostroboscopy, with vocal fold description following the guidelines of the ELS (32); (iii) an independent phoniatrist evaluates the voice using the RBH (roughness, breathiness, hoarseness) scale; (iv) all patients provide self-reported outcomes via the Voice Handicap Index-12.

As previously stated, the pathophysiological reasons for voice alterations in patients with HF remain unclear. The considerable number of patients participating in the *Strobo* sub-study will enable the provision of innovative insights into the pathophysiological aspects of disturbed vocal cord function and its potential association with prognosis, including rehospitalization and mortality within six months. Furthermore, the quality of voice recordings can vary due to factors such as ambient noise, the distance between the mouth and microphone, and the type of smartphone used by the patient after discharge (34). To assess and compare these impacts, simultaneous voice recordings were collected using both a smartphone and the reference standard of voice field measurement.

The importance of digital health technology in clinical trials is increasing (35, 36). Our study encompasses the development of a dedicated mobile solution and deploys smartphone-based remote data collection, allowing for asynchronous and continuous data collection in both hospital and home settings. The results from the AHF-Voice study will inform future decentralized and virtual clinical trials. Furthermore, vocal biomarkers may serve as a novel digital endpoint in future HF trials.

The study has several limitations. First, selection bias may affect the generalizability of the findings, as only German-speaking participants were included, which limits the applicability of the results to non-German speakers. Further studies should be conducted in additional languages in order to gain a more comprehensive understanding of the impact of language. Alterations in voice quality resulting from upper respiratory infections during the study period could confound the analysis of vocal biomarkers. For this purpose, a longitudinal data collection approach was chosen, and clinical (e.g., fever) and laboratory parameters (e.g., C-reactive protein) of inflammation assessed at each study visit. Finally, it is possible that participants' increased awareness of potential voice disorders, due to their involvement in the study, may influence their self-assessments of their voice.

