## Abstract

Acute heart failure (AHF) is a life-threatening condition and a common cause of hospitalization. The defining clinical feature of AHF is volume overload, leading to pulmonary and peripheral edema and consequently to weight gain. Vocal biomarkers have the potential to facilitate the early detection of worsening HF and the prevention of AHF episodes by offering a non-invasive, low-barrier monitoring tool. The AHF-Voice study is a prospective monocentric cohort study designed to investigate the trajectories of voice alterations during and after episodes of AHF, identify potential vocal biomarkers, and enhance the understanding of the pathophysiological mechanisms underlying these voice changes. It will examine the characteristics and determinants of vocal biomarkers, analyzing their correlations with patients' clinical status and comparing them to alternative clinical parameters in HF. Further, it aims to determine whether specific vocal biomarkers can accurately map different HF phenotypes and assess their association with patient trajectories**.** The study phenotypes patients hospitalized for AHF at admission and discharge, and follows them for a period of 6 months. During hospitalization, daily voice recordings are collected using a specially-designed smartphone app. Following discharge, patients are requested to continue daily voice recordings with their own smartphone for the subsequent six months the 6-month follow-up. Patient-reported outcome measures and body composition are assessed in the hospital and at follow-up visits. Sub-studies explore vocal fold oscillation through video-laryngostroboscopy and assess the feasibility of combining voice analysis with in-ear sensor technology for comprehensive digital phenotyping. A total of 131 patients were enrolled between April 2023 and November 2024: their mean age was 75 years (SD 10), 31% were women, 86% were in NYHA functional class III or IV, and 38% presented with *de novo* heart failure. Additionally, 59% of participants owned smartphones. The AHF-Voice study will provide insights into the potential of vocal biomarkers as reliable indicators of congestion, paving the way for innovative and accessible tools to support heart failure management.

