### Setting

All patients hospitalized at the Department Internal Medicine I of the University Hospital Würzburg are screened for study participation. The study period will be 6 months after index hospitalization, including structured follow-up visits after 6 weeks and 6 months. Figure 1 shows the study design. In addition to the primary study, two sub-studies will be conducted: the *Strobo* sub-study and the *In-Ear* sub-study.

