### Smartphone application

The smartphone application has been developed specifically for voice recording in the study. The app is available for iOS and Android systems and was developed through an iterative process that actively involved patients with HF in dedicated focus groups. Their feedback was incorporated into the design of the user interface to create a user-friendly and easy-to-use application (see Figure 2).

During index hospitalization, all patients are asked to perform daily voice recordings with a study smartphone (iPhone SE 2023, Apple Inc., Cupertino, USA) under the supervision of the study staff. Patients are then prompted through a voice dialogue interface on the smartphone app to perform the following set of speech tasks:
•Sustained vowel phonation (vowel/a:/)•Spontaneous speech•Reading standardized passage (“Northwind and Sun”)During index hospitalization, study staff ensures that the same time of day is chosen for the daily voice recordings (e.g., 30 min–1 h after waking up). After discharge, patients will be asked to continue using the smartphone app on their own smartphone, if available. These patients will be instructed to install the smartphone app on their device prior to discharge, and will then be prompted to perform the speech tasks once a day. In addition, the daily weight measurements can be entered into the app. During the follow-up period, patients who do not own a smartphone will not collect voice recordings after discharge, but will contribute to the data set when attending the outpatient visits after 6 weeks and 6 months.

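### The fever and CRP checks cited against confounding by respiratory infection fall on only two days of a six-month daily home recording period, so they do not cover the home recordings

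*Protocol article*

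**What the plan says.** - **Discussion, limitations paragraph:** "Alterations in voice quality resulting from upper respiratory infections during the study period could confound the analysis of vocal biomarkers". Two answers follow. One is that patients are followed over time; the other is to have "clinical (e.g., fever) and laboratory parameters (e.g., C-reactive protein) of inflammation assessed at each study visit".
- **Setting:** "The study period will be 6 months after index hospitalization, including structured follow-up visits after 6 weeks and 6 months".
- **Smartphone application and Abstract:** after discharge, patients who own a smartphone "will then be prompted to perform the speech tasks once a day"; the Abstract gives the length, in that "patients are requested to continue daily voice recordings with their own smartphone for the subsequent six months". Beyond the speech tasks, "In addition, the daily weight measurements can be entered into the app". No symptom or temperature entry is described.
- **Follow-up period:** admissions between visits are traced through discharge letters, and causes of death are clarified. A missed visit is replaced by a telephone interview with a shortened data set.
- **Figure 1 legend and Results:** the in-ear sensor, which measures temperature, belongs to a sub-study of 31 patients and is used in hospital and at the two visits.
- **Table 1:** 77 of 131 patients (59%) own a smartphone and can record at home.
- **Discussion and Conclusion:** the six-month recordings are to be related to disease progression, outcomes and prognosis, with early detection of decompensation as a longer-term objective.

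**The concern.** Voice is measured daily at home, and an infection can start on any of those days, but the infection check is tied to the visits. A cold that begins and ends between visits leaves no fever or CRP record beside the recordings it altered.

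Longitudinal collection does not close the gap by itself. Following each patient over time removes stable differences between patients, but infection varies within a patient. A cold and a decompensation can both appear as a departure from that patient's own baseline. The Introduction lists hoarseness and more irregular phonation among the suggested effects of congestion, so the two may also sound alike.

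The home trajectory and prognosis analyses are what is at stake. An unlabelled infection unrelated to outcome adds noise and weakens an association. One that also precedes an admission could produce a voice–outcome association that does not reflect congestion.

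**Working it through.** The article states no detection figure, so there is none to reproduce. The one input that can be checked agrees: 77/131 = 58.8%, reported as 59%.

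**Inputs**
- Visits at 6 weeks and 6 months (Setting), taken as day 42 and day 182.
- Home recording daily over the same period (Smartphone application, Abstract), taken as days 1 to 182.
- Illness duration D: not in the article; varied from 5 to 28 days.
- Onset: assumed equally likely on each of days 1 to 182.
- An episode counts as seen if it is active on day 42 or day 182.

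**Coverage of days.** 2/182 = 1.1% of home days are visit days, and the gap between the visits is 182 − 42 = 140 days.

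**Coverage of episodes.** An episode starting on day *a* is active from *a* to *a* + D − 1. For D up to 42, exactly D onset days reach the first visit and D others reach the second. So P(seen) = 2D/182 and P(unseen) = 1 − 2D/182.

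| Assumed D (days) | Seen | Unseen |
|---|---|---|
| 5 | 10/182 = 5.5% | 94.5% |
| 7 | 14/182 = 7.7% | 92.3% |
| 10 | 20/182 = 11.0% | 89.0% |
| 14 | 28/182 = 15.4% | 84.6% |
| 21 | 42/182 = 23.1% | 76.9% |
| 28 | 56/182 = 30.8% | 69.2% |

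**Break-even.** Above 42 days only 42 onset days can reach the first visit, so P(seen) = (42 + D)/182. This equals one half at D = 91 − 42 = 49 days. Within the assumed range, most episodes are missed at every duration.

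**Direction of the simplifications.** The count favours the plan in two ways. It treats every illness active on a visit day as detected, even if temperature and CRP are normal that day. It also assumes both visits are attended in person, although a telephone interview cannot measure CRP.

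**Other channels described.** Discharge letters cover infections that lead to admission. Voluntary weight entries give a partial contrast between fluid gain and a voice change without it. The in-ear sensor is not used at home. None of these labels an infection managed at home with its dates.

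**The case against.** The strongest reply is that a condensed article need not list every question asked at a visit. The follow-up assessments are not presented as complete, fever is given only as an example, and an infection history may be on the case report form. Infection is also disclosed as a limitation, and Future statistical analyses says confounding will be considered for each research question. This stands as far as it goes, and the absence of such a question is not the finding. The finding is that the article puts forward a particular safeguard, and on its own schedule that safeguard does not reach the home period.

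A second reply is that longitudinal data help. The Introduction describes worsening heart failure as gradual volume gain, so a brief voice change without weight gain is partly distinguishable. That is right in part, where weight is entered.

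Two stronger readings are tempting, and the article does not support them:
- **That infection inflates the voice–congestion association.** Between visits the only congestion marker described is weight entered in the app. The other surrogates fall at admission, discharge or visits, the occasions when inflammation is said to be checked. An infection that changes voice but not weight would tend to weaken the association.
- **That the main in-hospital result is compromised.** The machine-learning derivation primarily contrasts decompensated with recompensated states. In-hospital recordings are supervised and asked of all patients, and routine laboratory tests are listed at admission and discharge. That contrast is less exposed.

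**Conclusion.** The concern holds for the home period. The visit-based fever and CRP check does not cover the daily recordings of up to 77 patients: about 69% to 95% of episodes would be active on neither visit day. This rests on an assumed duration of 5 to 28 days, uniform onset, and visits at days 42 and 182.

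A reader might take those percentages as a measure of bias. They are not. The article gives no infection incidence, no share of recordings affected and no effect of infection on the voice measures, so the size and direction of any bias are unknown. Nor does the count show that infections cannot be recovered from patient recall or discharge letters. It shows that the cited check will not supply them. The point is worth acting on because the trajectory and prognosis aims use these recordings and the remedy is cheap.

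**What to change.** 1. **Follow-up still running:** add one yes/no item to the daily app prompt, for example *cold, sore throat or fever today?* Leave out hoarseness and cough, because either may itself reflect congestion.
2. **Follow-up otherwise:** ask a standard question on infections since the last contact, with approximate dates, at the visits or in the telephone interview. Take infection dates from the discharge letters already requested.
3. **Sensitivity analyses:** repeat the home-trajectory and prognosis analyses without flagged recordings, and with calendar month or season as a covariate. Enrolment from April 2023 to November 2024 plus six months runs to about May 2025, so the cohort spans two winters while each patient contributes only six months.
4. **Wording:** state in the limitations paragraph that visit-based fever and CRP do not cover the home period.

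Do not extend this to excluding in-hospital recordings by fever or raised CRP. Table 1 gives a baseline CRP of 1.0 [0.4; 2.5] mg/dl, so any cut-off at or below 1.0 would flag about half of the patients or more. It could selectively remove admission recordings, which represent the decompensated state.

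Cost: a slight daily burden, imprecise recalled dates where follow-up is complete (the gap between visits is about 140 days), and some recordings lost in the sensitivity analysis.

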## Conclusion

The AHF-Voice study provides a comprehensive framework deriving vocal biomarkers from voice recordings, covering all four dimensions of voice diagnostics: self-reported outcomes, physician-reported assessments, visual evaluation of the vocal cords, and acoustic voice analyses. The longitudinal design of the study permits the continuous monitoring of the voice over time, thereby offering valuable insights into the trajectories of voice alterations and their association with disease progression and prognosis in patients with HF experiencing an AHF episode. Moreover, the investigation aims to explore the potential of vocal biomarkers as a future tool for telemonitoring, with the objective to enable the early detection of decompensation in HF patients. In addition, the AHF-Voice study will inform on the utility of vocal biomarkers as digital endpoints for future HF trials.

## Data Availability

The original contributions presented in the study are included in the article/Supplementary Material, further inquiries can be directed to the corresponding author.
